### Analysis of Secondary Endpoints

Changes in the secondary endpoints will be analyzed with a non-parametrical test (Mann-Whitney U) Effect of the active treatment is evaluated and presented with 95% confidence intervals.

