### Secondary Endpoints

Secondary efficacy parameters are changes in quality of life compared to baseline level. The European Organization for research and treatment of cancer quality of life questionnaire (QOLQ, Bloechle *et al.* 1995 [23], will be used. Also the tolerability of the drug in this patient population will be compared to placebo.

In the experimental part of the study the difference of the QST stimulus are considered secondary efficacy parameters. The experimental baseline recordings will also be compared to published normal values from healthy controls to evaluate general aspects of pain processing in the patient group.

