## Randomization Criteria

Subjects will be randomized to the study providing they fulfill all of the entry criteria at screening. A computer-generated pseudo-random code will be used to assign subjects to treatment. For the groups there will be 2 randomization lists; one for diabetic patients and one for non-diabetic patients. This is to ensure an even distribution of diabetic and non diabetic patients in the placebo group and the pregabalin group. Individual treatment codes in sealed envelopes, indicating the treatment randomization for each randomized patient, will be available to the investigator(s) at the study centre. The individual treatment codes must not be broken except in medical emergencies when the appropriate management of the patient necessitates knowledge of the treatment randomization.

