## Screening

Visit 1; Screening (28 – 7 days before the first dose of study drug):

- Obtain informed consent.
- Physical examination.
- General and specific medical history (including drug/alcohol/tobacco consumption).
- Concomitant medication.
- Questionnaires (QOLQ, mBPI-sf, PD-Q and PGIC) are filled out.
- Blood and urine for hematology, clinical chemistry and urinalysis.
- Pregnancy test (urine) will be done in females not postmenopausal for more than 1 year or not sterile.
- 12-lead ECG.
- Blood pressure and pulse rate (supine and standing). Supine BP/PR should be measured following resting for 5 minutes. Standing BP/PR should be measured following standing for 2 minutes.
- Diary instruction. The patient will start completing the pain diary 7 days prior to the first dose of study drug.
- Experimental testing (training): pressure and electrical stimulation (skin and muscle) as described below.
- Cold pressor test (training) as described below.

Patients fulfilling inclusion and exclusion criteria are randomized and invited to join the study.

The duration time of the first visit will be approximately 4 hours.

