## Study Period

Seven days prior to the first dose of study drug, the patients will start to score pain levels in a pain diary. The average pain over the previous 24 hours and the worst pain over the previous 24 hours will be assessed using the VAS score. Usage of pain medication will also be recorded in the diary

Visit 2:

Day 1, first dose of study drug:

The patients visit the clinic and are instructed to start the trial medication if laboratory tests are normal. Ahead of the first dose of study drug the patients will undergo multimodal testing. They will have the skin in segments C5, T4, T10, L1 and L4 stimulated electrically. Also deep muscle pain will be assessed on the same places, using pressure stimulation. A cold pressor test is performed on the right hand and the deep muscle pain is measured on the left thigh both before and after the cold pressor test. Pain thresholds will be assessed using visual analogue scales (VAS).

These assessments are done before starting the treatment on Day 1 and on Day 21 + 14 days.

Patients will start the trial medication and score pain levels in the diary with a VAS value for the average pain over the previous 24 hours and a second VAS value for the worst pain over the previous 24 hours. Use of as needs pain medication will also be recorded in the diary.

The duration time of the second visit will be approximately 2 hours.

Telephone interviews

On days 4, 7, 11, 14 and 17 a study nurse or doctor will call the patients to assess the severity and tolerability of any adverse events.

On Day 7 a study nurse or doctor will call the patients to assess the adverse events and to administer the PD-Q and PGIC questionnaires. The dose of study drug will be discussed. Patients with acceptable adverse events will increase the dose to 300 mg BID. Patients experiencing unacceptable adverse events on 150 mg BID will be taken out of the study and will be replaced.

Visit 2:

All patients will visit the centre on day 21 + 14 days.

- Physical examination.
- Concomitant medication
- Questionnaires (QOLQ, mBPI-sf, PD-Q and PGIC) are filled out.
- Blood and urine for haematology, clinical chemistry and urinalysis.
- Pregnancy test (urine) will be done in females not postmenopausal for more than 1 year or not sterile.
- Experimental testing as described in visit 1: pressure and electrical stimulation (skin and muscle).
- Cold pressor test.

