### Analysis of Primary Endpoint

All participants who have received the study medication for at least 2 weeks will be included in the analyses. Dropouts are replaced and excluded from further analyses.

All endpoints are described and presented graphically. Primary endpoints will be subjected to analysis of covariance (ANCOVA), to permit analysis of confounding variables to be included. Effect of the active treatment is evaluated and presented with 95% confidence intervals.

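### The unadjusted, unstratified Mann-Whitney U on change scores for secondary endpoints is valid but gives up power that baseline and stratum adjustment would mostly recover

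*Protocol*

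**What the plan says.** The protocol's Analysis of Secondary Endpoints commits to one method: "Changes in the secondary endpoints will be analyzed with a non-parametrical test (Mann-Whitney U". It names no covariate and no stratification factor, and adds: "Effect of the active treatment is evaluated and presented with 95% confidence intervals".

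The endpoints concerned are listed under Secondary Endpoints. For the clinical part: "Secondary efficacy parameters are changes in quality of life compared to baseline level". For the experimental part: "In the experimental part of the study the difference of the QST stimulus are considered secondary efficacy parameters". Tolerability is listed there too.

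Both efficacy measures have a pre-treatment value. At Screening, "Questionnaires (QOLQ, mBPI-sf, PD-Q and PGIC) are filled out", and this is repeated at the final visit. For the sensory tests, Study Period says: "These assessments are done before starting the treatment on Day 1 and on Day 21 + 14 days".

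Under Randomization Criteria the allocation is stratified: "For the groups there will be 2 randomization lists; one for diabetic patients and one for non-diabetic patients". For the primary endpoints the protocol takes a different route: "Primary endpoints will be subjected to analysis of covariance (ANCOVA), to permit analysis of confounding variables to be included". It gives no reason for using adjustment in one place and not in the other.

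**The concern.** The choice of test is written into the protocol, so it is not a detail left open. It makes weak use of two pieces of information that the trial already has.

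- **Baseline.** Subtracting the baseline is the same as assuming a slope of 1 between baseline and end value. If the true correlation is moderate, the change score carries baseline noise that a fitted slope would remove.
- **Stratum.** Patients are balanced on diabetes by design, but the test does not use that factor. If diabetes predicts outcome, its contribution stays in the residual variation.

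Precision on the secondary endpoints is at stake. The protocol states no power for any of them, and the trial is small: 48 completers in Sample Size Determination, 60 in Subject Selection and Subject Withdrawal.

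**Working it through.** **No figure to reproduce.** The power figures under Sample Size Determination concern pain VAS, not the secondary endpoints. The inputs below are therefore partly assumed.

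**Inputs.** From the protocol: the test, the availability of baseline and stratum, and about 30 per arm (60 completers) or 24 per arm (48 completers). Assumed: two-sided alpha 0.05, a true shift of 0.5 SD, a baseline-to-end correlation r from 0.3 to 0.9, equal SDs at both times (set to 1), and normal errors at first.

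**Formulas.**
- Variance of a change score: 2(1 − r).
- Residual variance under ANCOVA: 1 − r².
- Ratio, change to ANCOVA: 2(1 − r)/(1 − r²) = 2/(1 + r). This is the ratio of sample sizes for equal power.
- Mann-Whitney against a t test with normal errors: relative efficiency 0.955, so the full ratio is 2/(1 + r)/0.955.
- Power: Φ(δ/(σ√(2/n)) − 1.96), with n multiplied by 0.955 for Mann-Whitney.

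**Example, r = 0.5, n = 30.** ANCOVA: σ = √0.75 = 0.866, standard error 0.866 × √(2/30) = 0.224, 0.5/0.224 = 2.24, power 0.609. Mann-Whitney on change: σ = 1, n = 28.65, standard error 0.264, 0.5/0.264 = 1.89, power 0.473.

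| r | 2/(1 + r) | with 0.955 | power, Mann-Whitney on change | power, ANCOVA | loss (points) |
|---|---|---|---|---|---|
| 0.3 | 1.54 | 1.61 | 0.359 | 0.528 | 16.9 |
| 0.5 | 1.33 | 1.40 | 0.473 | 0.609 | 13.6 |
| 0.7 | 1.18 | 1.23 | 0.686 | 0.774 | 8.8 |
| 0.9 | 1.05 | 1.10 | 0.988 | 0.993 | 0.5 |

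With 24 per arm the powers are 0.298 against 0.443, 0.395 against 0.516, and 0.589 against 0.679 at r = 0.3, 0.5 and 0.7.

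**Simulation.** 4,000 runs per scenario, 30 per arm, shift 0.5 SD, 30% diabetic (assumed). Both ANCOVAs adjust for baseline and diabetes; the rank version uses ranks of the end value and of the baseline. Power with no diabetes effect:

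| errors | r | Mann-Whitney on change | ANCOVA | rank ANCOVA |
|---|---|---|---|---|
| normal | 0.3 | 0.33 | 0.51 | 0.48 |
| normal | 0.5 | 0.45 | 0.59 | 0.56 |
| normal | 0.7 | 0.67 | 0.75 | 0.70 |
| t, 3 df | 0.3 | 0.43 | 0.57 | 0.73 |
| t, 3 df | 0.5 | 0.59 | 0.67 | 0.77 |
| t, 3 df | 0.7 | 0.86 | 0.81 | 0.86 |
| lognormal | 0.3 | 0.51 | 0.62 | 0.94 |
| lognormal | 0.5 | 0.74 | 0.71 | 0.92 |
| lognormal | 0.7 | 0.96 | 0.81 | 0.94 |

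With normal errors the loss against ANCOVA is 18, 14 and 8 points, close to the formula. Rank ANCOVA recovers about 15, 11 and 3 of those points.

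**Stratum.** With normal errors and a diabetes effect of 0.5 SD, Mann-Whitney power moves from 0.45 to 0.44 at r = 0.5 and from 0.67 to 0.63 at r = 0.7. Adjusted ANCOVA stays at 0.58 to 0.59 and at 0.75.

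**Validity.** With no treatment effect, rejection rates were 0.038 to 0.051 across all three methods and all three error shapes.

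**The case against.** The best defence is robustness. Quality of life is a questionnaire score. Under the cold pressor section, pain is set to 10 after early withdrawal of the hand and immersion stops at 2 minutes, so some measures are capped. A rank test suits such data, and in the simulation it beat ordinary ANCOVA with lognormal errors (0.96 against 0.81) and with heavy tails (0.86 against 0.81), both at r = 0.7. This stands, and it means that ordinary ANCOVA should not be the general replacement. It does not rescue the unadjusted test. Rank ANCOVA keeps the protection and matched or beat Mann-Whitney in every scenario but one (0.94 against 0.96: lognormal, r = 0.7, no diabetes effect).

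A second defence is that the correlation may be high. Experimental Study calls the reliability of the tests excellent, and at r = 0.9 little is lost. That may hold for the sensory measures. The protocol gives no correlation for any endpoint.

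A reader might infer more than the documents support:
- *That baseline is ignored.* It is subtracted, which is inefficient but not the same thing.
- *That the test is invalid because randomisation was stratified.* The simulated type I error does not show this.
- *That all sensory measures are affected.* Primary Endpoints makes pain tolerance thresholds in the dermatomes the experimental primary endpoint, so these fall under ANCOVA. Tolerability has no baseline to adjust for.
- *That the p-value and interval will come from different methods.* The protocol does not say so. A Hodges-Lehmann interval goes naturally with Mann-Whitney, and the estimator may be named in the SAP.
- *That the unnamed covariates of the primary ANCOVA are part of the fault.* A covariate list is commonly left to the SAP, and this point does not depend on it.

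**Conclusion.** The point holds as one of efficiency on secondary endpoints. The planned test is valid, and neither bias nor any effect on the primary conclusion is claimed. Under normal errors, a 0.5 SD shift, 30 per arm and r between 0.3 and 0.7, it gives up about 9 to 17 points of power against baseline-adjusted ANCOVA, or 8 to 18 in simulation. That equals needing about 1.6 to 1.2 times as many patients. Near r = 0.9 the power loss is negligible. Almost all of the loss comes from the fixed baseline slope; the omitted stratum costs up to about 4 further points in the scenarios at r = 0.5 and 0.7, and only if diabetes is prognostic. The correlation, shift, error shapes and diabetes prevalence are assumptions, so the figures give a range and not an estimate for this trial. The loss is avoidable because the variables needed are already collected.

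**What to change.** For secondary endpoints with a baseline (quality of life, and sensory-test measures other than the primary dermatome pain tolerance thresholds), replace the Mann-Whitney U as follows:

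1. Default, in particular for ordinal, capped or skewed measures: rank ANCOVA of the end-of-treatment value on treatment, with the endpoint's own baseline (ranked) and diabetes stratum as covariates.
2. Where an endpoint is pre-specified as approximately normal: ordinary ANCOVA with the same terms.
3. Take the 95% confidence interval from an estimate with the same adjustment. For ANCOVA this is the adjusted mean difference. For the rank version it could be a Hodges-Lehmann shift computed on residuals after removing baseline and stratum.

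Name in advance which endpoints follow which route. Tolerability is outside this change.

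The cost is a few sentences of protocol text and slightly more analysis work; no patients, visits or measurements are added. The one risk is using ordinary ANCOVA on skewed or heavy-tailed data, where it can do worse than a rank test. That is why the rank version should be the default.

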## Safety Analysis

No formal analyses are planned for safety data. These data (adverse events, vital signs and routine laboratory tests) will be explored through the use of standard presentations of descriptive statistics.

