#### Recording of adverse events

Information about adverse events will be collected from the first administration of any investigational product until the end of the study. Adverse events spontaneously reported by the patient and/or in response to an open question “have you had any health problems during the study since previous visit” from the study personnel or revealed by observation will be recorded at each visit from the first administration of any investigational product until the end of the study.

Any deterioration in laboratory values and vital signs need not be reported as AEs. However, abnormal values that meet criteria for an SAE or cause discontinuation of investigational product must be reported as SAE or AE and recorded in the CRF.

The time/date when the AE started and disappeared, maximum intensity, action taken with regard to investigational product, causality rating (yes or no), outcome, if AE caused patient to discontinue the study and whether or not it constitutes an SAE will be reported in the CRF for each AE.

The causality of non-serious AEs (i.e., their relationship to investigational product) will be assessed in the same way as for SAEs.

The intensity rating is defined as:

1 = mild (awareness of sign or symptom, but easily tolerated)

2 = moderate (discomfort sufficient to cause interference with normal activities)

3 = severe (incapacitating, with inability to perform normal activities)

It is important to distinguish between serious and severe AEs. Severity is a measure of intensity whereas seriousness is defined by the criteria as described above. An AE of severe intensity need not necessarily be considered serious. For example, nausea that persists for several hours may be considered severe nausea, but not a SAE.

Any AE not resolved at the last assessment or discontinuation of the study will be followed up within two weeks and thereafter as long as the investigator consider necessary.

The same parameters as for AEs / SAEs will be recorded in the case a SUSAR should occur during the study period.

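### Vital signs are named as safety data to be summarised, but blood pressure and pulse are explicitly scheduled only at screening, so no on-treatment blood pressure is required

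*Protocol*

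**What the plan says.** The Safety Analysis section plans no formal testing. It states: "These data (adverse events, vital signs and routine laboratory tests) will be explored", and limits this to descriptive summaries. Safety and tolerability are secondary objectives (section 2.1), and section 2.2.2 compares tolerability with placebo.

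Section 6.1 places the vital-sign measurement at "Visit 1; Screening (28 – 7 days before the first dose of study drug"). The item reads "Blood pressure and pulse rate (supine and standing"), and the conditions are fixed: supine after 5 minutes of rest, standing after 2 minutes.

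Section 8, Recording of adverse events, gives a reporting rule: "Any deterioration in laboratory values and vital signs need not be reported as AEs". The exceptions are abnormal values that meet the criteria for a serious event or that lead to stopping the investigational product.

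For Day 1, section 6.2 says: "Ahead of the first dose of study drug the patients will undergo multimodal testing". Five telephone interviews follow, on days 4, 7, 11, 14 and 17, and their purpose is stated as: "a study nurse or doctor will call the patients to assess the severity and tolerability of any adverse events". The laboratory item for the final visit is "Blood and urine for haematology, clinical chemistry and urinalysis". That visit is headed Visit 2 for a second time, although the text after its list calls it the third visit.

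**The concern.** A descriptive safety summary is useful when it shows what happened under treatment, by arm, against a starting value. Adverse events are collected from the first dose and laboratory tests are repeated at the end of treatment, so two of the three named data types can be summarised in that way. For the third, the text requires a reading before treatment and nothing to set beside it.

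Adverse event reporting would not reliably fill the gap. Under section 8, a change in vital signs that is neither serious nor a reason to stop treatment need not be reported as an adverse event. The vital-signs summary is then the natural place for such a change to appear. With no blood pressure required after dosing, whether one exists would depend on each site's habit, and its timing and posture would not be standardised.

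**Working it through.** No figure in the protocol needs to be reproduced and no formula applies. The check sets the planned contacts against the two places where procedures are prescribed, the visit lists in sections 6.1 and 6.2 and the Schedule of Activities.

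**Step 1. Blood pressure and pulse, contact by contact.**

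| Contact | Visit list (6.1, 6.2) | Schedule of Activities |
|---|---|---|
| Screening | Listed, supine and standing | No row |
| Day 1, before first dose | Not listed | No row |
| Days 4, 7, 11, 14, 17 | Telephone calls | No row |
| Day 21 + 14 days, end of treatment | Not listed | No row |

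Required readings per patient are therefore 1 before treatment and 0 + 0 + 0 = 0 from Day 1 onwards.

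**Step 2. Could another listed item supply the data?**

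- *Physical examination at the final visit.* Section 6.2 lists one. However, section 6.1 lists physical examination and blood pressure with pulse as separate items, so in the protocol's own usage the first does not include the second. The schedule ticks physical examination at screening only.
- *ECG at end of treatment.* The schedule ticks an ECG at screening and at end of treatment. Exclusion criterion 4 takes heart rate from the 12-lead ECG, so a second ECG would give an on-treatment heart rate. It gives no blood pressure, and the protocol asks for no standing ECG. The ECG is absent from the final-visit list.

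That leaves no required on-treatment blood pressure, and a heart rate only where the site follows the schedule.

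**Step 3. Compare the visit lists with the schedule for the other safety items.**

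| Item | Screening list (6.1) | Schedule, screening | Final-visit list (6.2) | Schedule, end of treatment |
|---|---|---|---|---|
| ECG | Yes | Yes | No | Yes |
| Weight | No | Yes | No | Yes |
| Coagulation | No | Yes | No | Yes |
| Physical examination | Yes | Yes | Yes | No |
| Blood pressure and pulse | Yes | No | No | No |

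The table and the text disagree in both directions and at both visits. Blood pressure and pulse differ from the first three items in one respect: at end of treatment neither source asks for them.

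**The case against.** The strongest objection is that silence proves little here. The schedule omits even the screening blood pressure that section 6.1 requires, and the final-visit list omits items that the schedule ticks, so neither is exhaustive. Sites may well take blood pressure during the final physical examination. This stands to the extent that one cannot say the readings will not be taken. It does not supply a requirement, because every place where one could stand is silent after screening.

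Second, the Safety Analysis section promises only description, and tolerability against placebo rests mainly on adverse events, the five telephone calls and repeat laboratory tests. This also stands. A reader might infer that the safety objective fails, and the protocol does not support that: one component of the summary is affected.

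Third, the sentence in section 8 about deterioration is a reporting exemption. A deterioration could come to light at one of the follow-up consultations that section 6.3 allows. The sentence therefore fits awkwardly with a single scheduled reading but does not prove that a scheduled repeat was intended.

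Fourth, the mismatch could be resolved equally well by deleting vital signs from the analysis text. That is a fair alternative, and the fix includes it.

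**Conclusion.** The point holds as an inconsistency of minor weight. The protocol names vital signs as safety data but explicitly schedules blood pressure and pulse only before treatment. For every patient the number of required on-treatment blood pressure readings is zero. The number of scheduled on-treatment heart rates is at most one, from an ECG that the schedule includes and the final-visit list leaves out. Counting that heart rate as a vital sign is itself an interpretation, since the Safety Analysis section does not name the ECG. No efficacy endpoint, sample size or inference is affected. This is not detail that can be left to an analysis plan, because such a plan can define a summary but cannot create the measurement.

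Three stronger readings are tempting and go too far.

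- *No on-treatment vital-sign data will exist.* The documents show only that none is explicitly required for blood pressure, and the schedule does provide an ECG heart rate.
- *The screening reading is useless.* It describes the patients at baseline and can inform the investigator's judgement of eligibility under exclusion criterion 1.
- *End-of-treatment ECG, weight and coagulation will be lost.* The schedule still requires all three. This is a mismatch between table and text, and for weight and coagulation it affects the screening list as well.

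The conclusion assumes that the visit lists and the schedule are the only places that prescribe procedures. The protocol as supplied shows no other.

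**What to change.** Add supine and standing blood pressure and pulse, measured under the conditions already given in section 6.1, to the final-visit list in section 6.2. Add a matching row to the Schedule of Activities, ticked at screening and at end of treatment. This gives each patient who attends the final visit a paired reading, and the vital-signs summary can then be shown by arm with change from screening. The cost is a few minutes per patient, at a visit planned for about 3 hours that already lists a physical examination.

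If the sponsor prefers not to add the measurement, remove vital signs from the Safety Analysis section, so that the plan does not announce a summary it has not arranged to collect. That costs nothing in visit time but gives up the only planned view of non-serious changes in blood pressure.

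In the same edit, reconcile the visit lists with the schedule. ECG, weight and coagulation are missing from the final-visit list, weight and coagulation are missing from the screening list, and the final-visit physical examination is missing from the schedule. This is editorial, and adds no procedure that one of the two sources does not already prescribe.
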